**Secondary outcome variables**

- Knowledge, attitudes, and control towards IPV during pregnancy
- Knowledge: Good versus Poor Knowledge,
- Attitude: supportive versus not supportive attitude toward IPV
- Controlling behavior: yes versus no
- Women’s autonomy and self-efficacy

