**Emotional/psychological violence: a** pregnant mother will be asked the following three psychological violence questions: (i) “say or do something to humiliate her in front of another person”, (ii) "threat to hurt or harm her or someone she cares about,” and (iii) insult or make her feel bad about herself” in the last 12 months and during the most recent pregnancy (Abramsky et al., 2011). If the mother responds to one of these emotional or psychological IPV questions, it will be recorded as 1 = yes; otherwise, 0=no (she has not experienced any emotional or psychological intimate partner violence during this pregnancy).

**Social support: The** Oslo-3 Social Support Scale (OSSS-3) will be used to measure the social support of women. The OSSS-3 consists of three items assessing the level of social support among women. Pregnant women will be asked, **Oslo 1**: How many people are so close to you that you can count on them if you have great personal problems? The responses will be: 1. 'None, 2. ‘1–2’ 3. ‘3–5’ 4, ‘5+’; **Oslo 2:** How much interest and concern do people show in what you do? The responses will be "none."2 ‘little’ 3 ‘uncertain’ 4 ‘some’ 5 ‘a lot’ and **Oslo 3**: How easy is it to get practical help from neighbors if you should need it? The response will be 'very difficult. 2 ‘difficult’ 3 ‘possible’ 4 ‘easy’ 5'very easy. The sum scores range from 3 to 14. Then the sum scores will be categorized as 3–8 (**poor social support**), 9–11 (moderate**social support),** and 12–14 (strong**social support**).

**Knowledge of IPV:** couples will be asked about nine items of knowledge questions on IPV. Couples who scored about 75% or above of the correct answer will be scored as “good knowledge,” and those who scored less than 75% will be scored as “poor knowledge (Oche et al., 2020).

**Attitude towards IPV**: To measure attitude toward intimate partner violence during pregnancy, couples will be asked, “In your opinion, is a husband justified in hitting or beating his wife in the following situations?" (a) “If she goes out without telling him?” (b) “If she neglects the children?” (c) “If she argues with him?” (d) “If she refuses to have sex with him?” (e) “If she burns the food?” Responses of “supportive attitude toward IPVp” to one or more of the scenarios were coded 1; “not supportive attitude toward IPVp" to all scenarios was coded '0'. (Trott et al., 2017).

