| 605 | Forcing partner to have sex when he/she does not want to is sexual violence | | | | Yes………………………………….1  No…………………………………..2 | | | | | | | | | | | | | | |  | | |
| 606 | Forcing partner to do something sexual that he/she finds degrading or humiliating is sexual violence | | | | Yes………………………………….1  No………………………..………….2 | | | | | | | | | | | | | | |  | | |
| 607 | Belittling or humiliating a partner in front of other people is psychological violence | | | | Yes……………………………….….1  No…………………………………...2 | | | | | | | | | | | | | | |  | | |
| 608 | Intimate partner violence during pregnancy has adverse maternal and newborn outcomes | | | | Yes…………………………….…….1  No…………………………………...2 | | | | | | | | | | | | | | |  | | |
| 609 | Intimate partner violence is human right violation | | | | Yes……………………………….….1  No…………………………………...2 | | | | | | | | | | | | | | |  | | |
| 610 | **Attitude** | | | | | | | | | | | | | | | | | | |  | | |
| 611 | In your opinion, is a husband justified in hitting or beating his wife in the following situation   1. Yes 2. No | | | | | |  | | | | | | | | | | | | |  | | |
| 612 | If she goes out without telling him? | | | | | | 1 | | | | | | | | | | 2 | | |  | | |
| 613 | If she neglects the children? | | | | | | 1 | | | | | | | | | | 2 | | |  |  |  |
| 614 | If she argues with him? | | | | | | 1 | | | | | | | | | | 2 | | |  |  |  |
| 615 | If she refuses to have sex with him? | | | | | | 1 | | | | | | | | | | 2 | | |  |  |  |
| 616 | If she burns the food? | | | | | | 1 | | | | | | | | | | 2 | | |  |  |  |
| 617 | **Controlling behavior** | | | | | | | | | | | | | | | | | | |  |  |  |
|  | In your opinion, is the husband is justified in controlling you in the following situation?   1. Yes 2. No | | | | | | | | | | | | | | | | | | |  |  |  |
| 618 | Jealous if she talked with other men | | | | | | 1 | | | | | | 2 | | | | | | |  | | |
| 619 | Accused her of unfaithfulness | | | | | | 1 | | | | | | 2 | | | | | | |  |  |  |
| 620 | Did not permit her to meet her friends | | | | | | 1 | | | | | | 2 | | | | | | |  | | |
| 621 | Tried to limit her contact with family | | | | | | 1 | | | | | | 2 | | | | | | |  |  |  |
| 622 | insisted on knowing where she is | | | | | | 1 | | | | | 2 | | | | | | | |  | | |
| 623 | did not trust her with money | | | | | | 1 | | | | | 2 | | | | | | | |  |  |  |

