| 108 | What is your wife’s ethnicity | | Hadiya..................................................................1  Kembata...............................................................2  Silte......................................................................3  Amhara................................................................4  Others, specify.....................................................5 | | | | |  |  |
| 109 | What is your education level? | | No education.........................................................1  Attended elementary school(1-8).........................2  Attended junior or senior high school(9-12)…….3  Attended college or higher(tertiary)education…..4 | | | | |  |  |
| 110 | What is your wife’s education level? | | No education......................................................1  Attended elementary school(1-8).......................2  Attended junior or senior high school(9-12)…..3  Attended college or higher(tertiary)education...4 | | | | |  |  |
| 111 | What is your occupation? | | Farmer .................................................................1  Government employee.........................................2  Self-employed …………………………….........3  Others, specify......................................................4 | | | | |  |  |
| 112 | What is your wife’s occupation? | | Housewife.............................................................1  Government employee.........................................2  Self-employed …………………………….........3  Others, specify......................................................4 | | | | |  |  |
| 113 | What is your average family monthly income in Birr? | | Birr per month(estimate of the respondent)  ………………………………… | | | | |  |  |
| 114 | How many wives do you have? | | One ……………...……………………...….....1  Two and above……………...…………..........2 | | | | |  |  |
|  | **PART TWO: KNOWLEDGE, ATTITUDE AND CONTROLLING BEHAVIOUR QUESTIONS** | | | | | | |  | |
| 200 | **Knowledge** | | | | | | |  | |
| 201 | Have you heard of Intimate partner violence? | | | Yes----------------------------1  No-----------------------------2 | | | |  | |
| 202 | Media, hospitals, health center are examples of sources of information for intimate partner violence | | | Yes ………………………………….1  No …………………………………..2 | | | | 0 | |
| 203 | IPVp is a serious public health issue | | | Yes ………………………………….1  No …………………………………..2 | | | |  | |

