| 204 | Slapping, kicking, dragging, beating, choking, pushing, etc., are examples of IPV | | | Yes…………………………………..1  No …………………………………..2 | | | |  | |
| 205 | Forcing partner to have sex when he/she does not want to is sexual violence | | | Yes………………………………….1  No…………………………………..2 | | | |  | |
| 206 | Forcing partner to do something sexual that he/she finds degrading or humiliating is sexual violence | | | Yes………………………………….1  No………………………..………….2 | | | |  | |
| 207 | Belittling or humiliating a partner in front of other people is psychological violence | | | Yes……………………………….….1  No…………………………………...2 | | | |  | |
| 208 | Restricting a partner from contact with family or friends | | | Yes…………………………….…….1  No…………………………………...2 | | | |  | |
| 209 | Intimate partner violence is human right violation | | | Yes……………………………….….1  No…………………………………...2 | | | |  | |
| 210 | **Attitude** | | | | | | |  | |
|  | In your opinion, is a husband justified in hitting or beating his wife in the following situation?  1---------------Yes  2…………… No | | | | | | |  | |
| 211 | If she goes out without telling him? | Yes…………………………………….….…...1  No…………………………………….…….…2 | | | | | |  | |
| 212 | If she goes out without telling him? | Yes…………………………………….….…...1  No…………………………………….…….…2 | | | | | |  | |
| 213 | If she neglects the children? | Yes…………………………………….….…...1  No…………………………………….…….…2 | | | | | |  | |
| 214 | If she argues with him? | Yes…………………………………….….…...1  No…………………………………….…….…2 | | | | | |  | |
| 215 | If she refuses to have sex with him? | Yes…………………………………….….…...1  No…………………………………….…….…2 | | | | | |  | |
| 216 | **Controlling behavior** | | | | | | |  | |
|  | In your opinion, is the husband is justified in controlling his wife in the following  Situation? | | | | | |  | | |
| 217 | Jealous if she talked with other men | | | | 1 | 2 | |  | |
| 218 | Accused her of unfaithfulness | | | | 1 | 2 | |  |  |
| 219 | Did not permit her to meet her friends | | | | 1 | 2 | |  |  |
| 220 | Tried to limit her contact with family | | | | 1 | 2 | |  |  |
| 221 | insisted on knowing where she is | | | | 1 | 2 | |  |  |
| 222 | did not trust her with money | | | | 1 | 2 | |  |  |
|  | **PART THREE: Male Involvement in maternal health care (MHC)** | | | | | | |  | |
| 301 | Did your wife take ANC during her recent pregnancy at health facility? | Yes………………………………………..…...1  No……………………………………….….…2 | | | | | |  | |

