| 109 | | | | የትምህርት ደረጃዎት ስንት ነዉ? | | ትምህርት የለም.................................................1  አንደኛ ደረጃ ትምህርት ቤት (1-8)......................2  ሁለተኛ ደረጃ ት/ቤት (9-12)………………..….3  ኮሌጅ ወይም ከፍተኛ ትምህርት ተከታትሏል …...4 | | | | | | |  |  |
| 110 | | | | የባለቤቶት ትምህርት ደረጃ ምነድነዉ? | | ትምህርት የለም...................................................1  አንደኛ ደረጃ ትምህርት ቤት (1-8)..........................2  ሁለተኛ ደረጃ ት/ቤት (9-12)………………..…….3  ኮሌጅ ወይም ከፍተኛ ትምህርት ተከታትሏል ……...4 | | | | | | |  |  |
| 111 | | | | ሥራዎት ምንድነዉ? | | ገበሬ....................................................................1  የመንግስት ተቀጣሪ..............................................2  የግል ስራ………………….…………….…….......3  ሌላ, ይገለጽ.........................................................5 | | | | | | |  |  |
| 112 | | | | የባለቤቶት ስራ ምንድነዉ? | | የቤት እመቤት ...................................................1  የመንግስት ተቀጣሪ...........................................2  የግል ስራ………………….…………………......3  ሌላ, ይገለጽ......................................................5 | | | | | | |  |  |
| 113 | | | | አማካይ የቤተሰብዎ ወርሃዊ ገቢ በብር ስንት ነው?? | | ብር በወር (የመላሽ ግምት)……………………………… | | | | | | |  |  |
| 114 | | | | ስንት ምስት አሎት? | | አንድ…………...……..………………...….......1  ሁለትና ከዚያ በላይ ……………...……….........2 | | | | | | |  |  |
|  | | | | **ክፍል አራት : የእውቀት፣የአመለካከትና ባህሪ መቖጣተር ጥያቄዎች** | | | | | | | |  | | |
| 401 | | | ስለ የቅርብ አጋር ጥቃት ሰምተዉ ያዉቃሉ? | | | | | 1.አዎ  2.አላዊቅም | | | |  | | |
| 402 | | የቅርብ አጋር ጥቃት ላይ የመረጃ ምንጮች ምንድናቸው? | | | | | | **1.አዎ 2. አይደለም**  ሚዲያ …………………….…1 2  የግል ልምድ…………......……1 2  ሆስፕታል/ጤና ጣቢያ/ጤና ኬላ..1 2  ከጤና ኤክስቴንሽ ባለሙያዎች…..1 2  ከሌክተር…………………....1 2 | | | |  | | |
| 403 | | የቅርብ አጋር( ጥቃት የህዝብ ጤና ጉዳይ ነው። | | | | | | አዎ ………………………………….1  አይደለም……………..……………..2 | | | |  | | |
| 404 | | በጥፊ መምታት፣ መምታት፣ መጎተት፣ መደብደብ፣ ማነቆ፣ መግፋት፣ ወዘተ.የፍቅር አጋር ጥቃት ምሳሌዎች ናቸው። | | | | | | አዎ ………………………………….1  አይደለም……………..……………..2 | | | |  | | |
| 405 | | የትዳር አጋሮ ባልፈለገች ጊዜ ወሲብ እንዲፈጽም ማስገደድ ወሲባዊ ጥቃት ነው። | | | | | | አዎ ………………………………….1  አይደለም……………..……………..2 | | | |  | | |
| 406 | | እሱ/እሷ የሚያዋርድ ወይም የሚያዋርድ ነገር እንዲፈጽም ማስገደድ ወሲባዊ ጥቃት ነው። | | | | | | አዎ ………………………………….1  አይደለም……………..……………..2 | | | |  | | |
| 407 | | አጋርን በሌሎች ሰዎች ፊት ማዋረድ ወይም ማዋረድ የስነ ልቦና ጥቃት ነው። | | | | | | አዎ ………………………………….1  አይደለም……………..……………..2 | | | |  | | |
| 408 | | በእርግዝና ወቅት የቅርብ ወዳጃዊ ጥቃት የእናቶች እና አዲስ የሚወለዱ ሕፃናት ላይ አሉታዊ ውጤቶች አሉት፡፡ | | | | | | አዎ ………………………………….1  አይደለም……………..……………..2 | | | |  | | |

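### The husbands' questionnaires do not carry the wives' nine knowledge items, so the single 75% knowledge score in section 6.17 does not measure common content

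*Protocol*

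**What the plan says.** The list of secondary outcomes in section 6.6.1 includes "Knowledge: Good versus Poor Knowledge". Section 6.17 defines it once for both partners: "couples will be asked about nine items of knowledge questions on IPV", and "Couples who scored about 75% or above of the correct answer will be scored as" having good knowledge, with anything below 75% poor. Section 5.3.2 makes couples' knowledge part of the third specific objective.

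The annexed forms each have nine numbered knowledge items: 601–609 for wives (Annex II in English, Annex VI in Amharic), 201–209 for husbands in English (Annex III) and 401–409 for husbands in Amharic (Annex vii). Two positions do not agree:

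- **Item 8.** Wives are asked whether "Intimate partner violence during pregnancy has adverse maternal and newborn outcomes" (608). The Amharic husbands' form asks the same (408). The English husbands' form has instead "Restricting a partner from contact with family or friends" (208).
- **Item 2.** The English husbands' form has one yes/no statement, "Media, hospitals, health center are examples of sources of information for intimate partner violence" (202), and both wives' forms have the equivalent (602). The Amharic husbands' form asks an open question, "የቅርብ አጋር ጥቃት ላይ የመረጃ ምንጮች ምንድናቸው" (what are the sources of information on partner violence), followed by five separate yes/no lines: media, personal experience, health facility, health extension worker and lecturer (402).

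Section 6.21 makes the English questionnaire the source for the Hadiyisa translation. Section 6.22 speaks of an Amharic translation.

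**The concern.** One item count and one cut-off for both partners imply one set of items. The forms do not supply it.

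Item 208 is a noun phrase without a predicate, so the form does not say what a yes affirms, and the protocol's own definitions do not settle it. Restricting contact is not among the acts of psychological violence in section 6.17 or in the Annex V handout. Section 6.17 places it under controlling behaviour, a separate secondary outcome, and the same husbands' form asks about friends and family again there (items 219 and 220). Item 402 has no stated way to turn five answers into one mark.

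The item lost from the English husbands' form is the only knowledge item on the maternal and newborn consequences of violence in pregnancy. Table 2 makes those consequences part of session 2. If the field version for husbands is a faithful translation of the English form, whatever husbands learn on this topic cannot enter their score.

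**Working it through.** **Inputs.** Nine items and a 75% cut (section 6.17); the item lists in Annexes II, III, VI and vii.

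**The plan's own cut-off.** 0.75 × 9 = 6.75, so at least 7 correct are needed: 7/9 = 77.8% passes and 6/9 = 66.7% fails.

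**Item match.** The other seven positions agree in content on all four forms. The two that do not:

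| Form | Item 2 | Item 8 |
|---|---|---|
| Wives, English (602, 608) | one statement | maternal and newborn harm |
| Wives, Amharic (602, 608) | one statement | maternal and newborn harm |
| Husbands, English (202, 208) | one statement | restriction of contact, no predicate |
| Husbands, Amharic (402, 408) | question with five yes/no lines | maternal and newborn harm |

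Shared items:

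- wives and husbands, English: 9 − 1 = 8
- wives and husbands, Amharic: 9 − 1 = 8
- English and Amharic husbands' forms: 9 − 2 = 7
- all four forms: 7

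**When the odd item decides.** Let s be the number correct among the 8 items shared with the wives' form. If s is 7 or 8, the husband passes whatever the odd item gives. If s is 5 or less, he reaches at most 6 and fails. If s = 6, he passes with 6 + 1 = 7 and fails with 6 + 0 = 6. So the odd item decides exactly when s = 6.

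**How much this could move the outcome.** The protocol gives no item-level rates, so this is an illustration under an assumption: independent items, each shared item correct with probability p and the odd item with probability q. Then

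P(good) = P(s ≥ 7) + P(s = 6) × q, with s binomial(8, p).

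For p = 0.7: P(s ≥ 7) = 8 × 0.7⁷ × 0.3 + 0.7⁸ = 0.255, and P(s = 6) = 28 × 0.7⁶ × 0.3² = 0.296.

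| p | q = 0.5 | q = 0.7 | q = 0.9 |
|---|---|---|---|
| 0.6 | 21.1% | 25.3% | 29.4% |
| 0.7 | 40.4% | 46.3% | 52.2% |
| 0.8 | 65.0% | 70.9% | 76.8% |

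Moving q from 0.5 to 0.9 changes the share with good knowledge by about 8 to 12 percentage points.

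**Scoring shared items only.** With 8 items, 0.75 × 8 = 6, so 6/8 = 75.0%. With 7 items, 0.75 × 7 = 5.25, so 6/7 = 85.7%. The effective threshold therefore shifts with the number of items kept.

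**The case against.** The strongest reply is that nothing planned fails. Each form has nine numbered items, so a score out of nine exists for each form once 208 has a key and 402 a marking rule, and such rules may sit in a statistical analysis plan that is not shown. Item 208 follows four items that classify acts as violence (204–207), so the missing predicate is easy to guess. Two of the options in 402 are sources that 202 and 602 themselves name, so marking it as one item is feasible. Both arms receive the same questionnaires at baseline and endline. The Hadiyisa form is not shown, and section 6.16 plans back-translation, an expert committee, content review and a pilot in 27 couples.

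Much of this stands, and it rules out several stronger readings that a reader might infer:

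- *That the score cannot be computed.* It can be, form by form. What is missing is one common score.
- *That two of nine items (22%) are lost for every husband, so that anyone with 5 or 6 of the other seven correct is undecided.* This adds defects from two different forms. It describes only the English against the Amharic husbands' form; against the wives, each husbands' form differs by one item.
- *That the Amharic form has 13 scored responses (8 + 5) and a cut of 10.* The protocol fixes nine items, and 402 is one numbered item.
- *That the trial's between-arm comparison is biased.* Identical forms in both arms do not produce that.

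Two things survive. A scoring rule written later can key 208, but it cannot recover an answer on maternal and newborn harm that was never asked. And back-translation compares each form with its own original; it does not compare the husbands' items with the wives', so it need not detect this mismatch.

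**Conclusion.** The point holds as a defect in the measurement of a secondary outcome. Section 6.17 sets one nine-item, 75% score for both partners, and no pairing of an annexed wives' form with an annexed husbands' form shares all nine items: 8 of 9 match within each language, and 7 of 9 between the two husbands' forms. The differing item decides the class of a husband with exactly 6 of the other 8 correct.

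The harm is to content validity, to comparability between spouses, and to the sensitivity of the English husbands' form to part of session 2. That session also covers economic and social consequences and triggers, so the loss is partial. The randomised comparison within husbands is not biased by this alone, provided both arms use the same language version. How far the defect reaches the data depends on which version is fielded, since the Hadiyisa form is not available. The percentage-point range rests on assumed independent items and assumed rates correct.

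**What to change.** Before the pre-test:

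1. In Annex III, replace item 208 with the statement in wives' item 608. The Amharic counterpart (408) already has it.
2. In Annex vii, replace item 402 with the single statement of 202/602. The Amharic text already exists as wives' item 602 in Annex VI.
3. Carry both corrections into the Hadiyisa version, and state in section 6.17 that both partners are scored on the identical nine items in every language.
4. If the item on restricting contact is wanted, complete its predicate and put it on both partners' forms. Whether it then counts towards the score is the investigators' choice, to be stated with the revised item count.

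This costs two questionnaire lines, one sentence in section 6.17 and no added interview time.

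If data have already been collected, score only the shared items (8 if one language version was used for both spouses, 7 if the forms were mixed), state the resulting cut (6 of 8 or 6 of 7) and report wives and husbands separately. This restores common content, but where the English husbands' wording was fielded it cannot restore the missing item.

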**6.21 Data collection instruments**

**Questionnaires**

**Quantitative study**: structured-interviewer-administered questionnaires adapted from the WHO multi-country study questionnaire will be used to collect information on intimate partner violence in pregnancy (WHO, 2010). The English version of the questionnaire will be translated into the local language (Hadiyisa) by fluent speakers. Then, the questionnaire's local language will be translated back to English by another expert to ensure consistency and accuracy. Four types of questionnaires will be administered at baseline and at the endline for couples (pregnant wife and husband). The data will be collected using a mobile-based application called KoBo Collect. The content of the information under each questionnaire will be as follows:

**Questionnaire for pregnant mothers at baseline and end-line**: the questionnaire will be administered to all pregnant women in the two groups (intervention and control groups) after obtaining informed verbal and written consent. The questionnaire contains individual characteristics of mothers, including age, levels of education, occupation, marriage type, parity, pregnancy intention, and household characteristics. Relational characteristics: duration of marriage and disparity in educational attainment

Moreover, the relational characteristics include the presence of social support and religion. The societal characteristics of pregnant women include women’s autonomy in addition to male involvement in antenatal care. All questionnaires will be administered to the intervention and control groups before any education session. Outcome measures: couples' knowledge, attitude, and control towards IPV; self-efficacy; pregnant women’s experience of IPV in the last 12 months and during the recent pregnancy

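### The English husbands' form asks one attitude scenario twice and leaves out burnt food; fielded uncorrected, it would score husbands on four scenarios instead of the five in section 6.17

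*Protocol*

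**What the plan says.** Section 6.6.1 lists attitude among the secondary outcomes, as a binary variable: "Attitude: supportive versus not supportive attitude toward IPV". Objective 3 in section 5.3.2 includes couples' attitudes.

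Section 6.17 defines the measure. Both partners are respondents: "To measure attitude toward intimate partner violence during pregnancy, couples will be asked". It lists five scenarios, (a) to (e), and the last is "If she burns the food". Support "to one or more of the scenarios were coded 1"; a code of 0 requires non-support in every scenario.

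The English husbands' form in Annex III has five attitude rows, 211 to 215. The first three are "211 | If she goes out without telling him", "212 | If she goes out without telling him" and "213 | If she neglects the children". Item 214 is about arguing and 215 about refusing sex. Item 216 is the heading of the controlling-behaviour block.

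On the field language, section 6.21 states: "The English version of the questionnaire will be translated into the local language (Hadiyisa) by fluent speakers". Section 6.16 also describes translation of the English instruments into Hadiyisa. Section 6.22 instead describes an Amharic version with back-translation.

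**The concern.** The form and the outcome definition disagree. Under an any-of rule a repeated question adds nothing, so Annex III can deliver only four of the five scenarios that 6.17 requires. The form still has five rows, so it looks complete at a glance.

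What is at stake is the validity of husbands' attitude, one part of a named secondary outcome. Section 6.17 gives a single scoring rule for couples. With the English forms as printed, wives would be scored on five scenarios and husbands on four. The lost item cannot be reconstructed from the other answers.

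**Working it through.** No sample size, power or error rate depends on this point, and the plan gives no figure to reproduce. The check is an item-by-item comparison of the scenarios in 6.17 with the printed forms. It goes by topic and does not assess the quality of the Amharic translation.

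| Scenario in 6.17 | Women, English (Annex II) | Husbands, English (Annex III) | Husbands, Amharic (Annex VII) |
|---|---|---|---|
| (a) leaves without telling husband | 612 | 211 and 212 | 410 |
| (b) neglects children | 613 | 213 | 411 |
| (c) argues | 614 | 214 | 412 |
| (d) refuses sex | 615 | 215 | 413 |
| (e) burnt food | 616 | none | 414 |
| Rows / different scenarios | 5 / 5 | 5 / 4 | 5 / 5 |

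**Not a reading artefact.** In Annex III the two identical rows carry their own consecutive numbers and response codes, and numbering runs unbroken from 211 to the heading at 216. No row has dropped out.

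**Effect on the score.** Let p5 be the share of husbands who support beating in at least one of (a) to (e), p4 the share for at least one of (a) to (d), and q the share who support it for (e) only. Then p5 = p4 + q. Since q cannot be negative, p4 is never above p5: the English form can lower measured support but cannot raise it. The shortfall is exactly q, and the documents give no item-level rates from which to obtain it.

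**Effect on the arm comparison.** The difference between arms on five scenarios equals the difference on four plus the difference between arms in q. With the same form in both arms, the omission matters to the contrast only as far as q differs between arms. The documents say nothing about that.

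**Would the planned checks find it?** The back-translation step in 6.16 compares the original English with the back-translated English. A duplicate in the original that is translated faithfully will agree perfectly. Cronbach's alpha, with its threshold of 0.7, tends to rise when an item is repeated, so it would not flag the error either. Expert review and the pilot could catch it, but no step is described that compares the forms with 6.17.

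**The case against.** The strongest counter-argument is that the loss is not established. The only translated husbands' form in the protocol, the Amharic one, has five different rows and asks about burnt food. No Hadiyisa form is shown, and sections 6.16 and 6.21 on one side and 6.22 on the other do not settle which language is fielded. This stands, and it makes the consequence conditional: it follows only if the English form, or an uncorrected translation of it, is used. It does not remove the error. English is the stated source for the Hadiyisa form. Nor is the Amharic husbands' form simply a corrected copy of the English: knowledge item 208 in Annex III concerns restricting contact with family or friends, while its counterpart 408 in Annex VII concerns adverse maternal and newborn outcomes. The two forms need reconciling in any case.

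Second, sections 6.16 and 6.22 plan an expert committee, content review, a pilot in 27 couples, a pre-test, and reliability and validity tests that include the attitude items. An interviewer who reads the same question twice in a row may well notice. This also stands: it is too much to say that the omission will reach the field. But these steps do not guarantee correction.

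Third, a reader might infer that husbands interviewed in Amharic would be asked five scenarios and those in Hadiyisa four, so that the outcome shifts with the language mix of the kebeles. The documents do not support this. They contain competing descriptions of the translated version, not a plan for a mixed-language survey. Data collectors must speak both languages (6.18), but the participants' choice of language is mentioned only for the education manual.

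Fourth, a husband-versus-wife comparison of attitude is not among the analyses in 6.24, which compares arms and before with after. The mismatch between the two forms is a matter of one outcome having two definitions, not a spoiled planned test.

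**Conclusion.** The English husbands' form is wrong as printed: it conflicts with 6.17, with the women's form and with the protocol's own Amharic husbands' form. If it, or a Hadiyisa form made from it, is fielded uncorrected, husbands' attitude becomes an any-of-four outcome. One of the five defined scenarios is lost (1/5 = 20% of the set), and measured support is lowered by the share of husbands who endorse burnt food alone.

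That share is not in the documents, so the size cannot be computed. A reader might put a count on it. With an assumed share of 1% to 5%, 216 husbands per arm would give 0.01 × 216 = 2.2 to 0.05 × 216 = 10.8 misclassified at baseline. After the planned 20% loss, 216 × 0.8 = 172.8 remain, giving 1.7 to 8.6 at endline. These counts are only the assumption multiplied out and are not evidence of impact.

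A reader might also infer a bias between arms. That does not follow from the omission itself, because the same form would serve both arms. The effect is on the validity and sensitivity of one secondary outcome. The primary outcome, which rests on women's reports, and the sample size are untouched. The point merits correction because the error is definite, cheap to remove beforehand and impossible to repair afterwards.

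**What to change.** In Annex III, delete the duplicate item 212, move the present items 213 to 215 up by one, and add "If she burns the food" as item 215. Items 211 to 215 then carry (a) to (e) in the order of 6.17, matching the sequence in the women's form and the Amharic husbands' form. Overwriting 212 in place would restore the content but leave a different order from the other forms.

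Carry the change into the Hadiyisa form and the KoBo form before the pre-test and baseline, and check each field form once against the list in 6.17. Timing matters: correcting the form between baseline and endline would change the definition within the before-and-after comparison planned in 6.24.

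The cost is one deleted row and one added row in the questionnaire and its electronic version. Nothing changes in design, sample size or analysis.
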